#### 15.4 DROP-OUT RATE

Drop-outs after V2 will be replaced until the required number of at least 400 subjects completing V2 and V3 is reached.

#### 15.5 ANALYSIS SETS

The statistical evaluation will be based on separate, hierarchically organized analysis sets as defined below:

- All subjects randomized set  
All subjects which were randomized to the treatment groups.
- All subjects treated set

All subjects of the all subjects treated set which received at least 1 dose of the IP.

- Full analysis set

All subjects in the all subjects treated set for which the primary endpoint is available. Subjects which have not been enrolled in the study according to the inclusion/exclusion criteria, but this had only been detected during the study or during the process of data cleaning will be excluded from the full analysis set but remain in the all subjects treated set (ICH E9, 1998)

- Per-protocol analysis set

All subjects of the full analysis set without any major violation of the protocol and its procedures. Major violations will be defined during the blind data review (see 15.6).

A flowchart will show the final disposition of all subjects in the different analysis sets according to the treatment groups together with a summary of the reasons for exclusion. Demographic and baseline characteristics will be analyzed for all four analysis sets. Analyses with respect to safety will be performed for the all subjects treated set. Analyses with respect to efficacy will be conducted both for the full-analysis set and the per-protocol analysis set. The data of subjects who were not randomized will be listed and documented at the site and stored in the ISF and TMF. They will not be entered in the clinical database or otherwise reported.

All subjects randomized will receive the IP, but will only start using it after onset of common cold symptoms. The decision of whether or not to begin treatment could not be influenced by knowledge of the assigned treatment, as the study is performed in a double-blind manner.

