### 10.4 EXCLUSION CRITERIA

1. Known allergy or hypersensitivity to the components of the investigational product

2. History and/or presence of clinically significant condition/ disorder (self-reported), which per investigator's judgement could interfere with the results of the study or the safety of the subject, e.g.:
  - Nasal disorder (e.g. polyposis, relevant septal deviation, ulcer etc.) and/or reconstructive surgery
  - Asthma, chronic obstructive lung disease or any other acute/chronic airways disease/disorder (e.g. chronic cough of any origin)
  - Acute psychiatric disorders
  - Any other acute/chronic serious organ or systemic diseases
3. Influenza vaccination within the last 3 months prior to V1 and during the study
4. Regular use of products that may influence the study outcome (e.g. immune suppressants/immune stimulants including natural health products, analgesics/anti-rheumatics, anti-phlogistics, anti-tussives/expectorants, mouth or throat therapeutics, decongestants, antibiotics, anti-histaminergic drugs, nasal drops/spray) within the last 4 weeks prior to V1
5. Pregnancy or nursing
6. History of (in the past 12 months prior to V1) or current abuse of drugs, alcohol or medication
7. Participation in the present study of a person living in the same household as the subject
8. Inability to comply with study requirements according to investigator's judgement
9. Participation in another clinical study in the 30 days prior to V1 and during the study

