## 12 CONCOMITANT TREATMENT

The subjects report use of any concomitant treatment (e.g. other medical devices, medication, any natural health products including food supplements etc.) to the investigator at the first visit. The investigator documents the following information in the CRFs: substance, dosage, start and duration, reason. Subjects will also be advised to inform the investigators of any treatment performed throughout the clinical investigation period.

During the study, the following concomitant treatment listed in the exclusion criteria should not be used:

- products that may influence the study outcome (e.g. immune suppressants/immune stimulants including natural health products, analgesics/anti-rheumatics, anti-phlogistics, anti-tussives/expectorants, mouth or throat therapeutics, decongestants, antibiotics, anti-histaminergic drugs, nasal drops/spray), except for the defined “rescue” treatment
- influenza vaccination.

The following treatment is defined as “rescue” medication during the period of common cold/ start of IP use until V3:

- paracetamol (max. 2 g/day),
- ibuprofen (max. 400 mg/day),
- saline nose drops or nose spray
- as well as antibiotics (in case they are medically required for another ailment following the confirmation of the bacterial infection, however not to be used for common cold).

At enrollment, the investigator informs the subjects that any concomitant treatment that could possibly influence the outcome of the study is not allowed, except for the defined rescue medication.

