### **13.8.1 Withdrawal of Subjects**

Reasons for subject's withdrawal may be for example:

- Serious adverse event (SAE)

- Intolerance of the investigational product
- Required additional therapy due to other complaints, which could influence the safety of the subject or the results of the study
- Clinically significant illness or intake of concurrent medication according to exclusion criteria, which could influence the results of the study
- Subject is not compliant with study requirements (according to investigator judgement)
- Withdrawal of informed consent
- Subjects in the study once the number of treated subjects has been completed

Reason, time and specific details of a subject's withdrawal are documented in the CRF. Each subject terminating the study prematurely will be asked to undergo the end-of-study visit, to be documented in the CRF, as follows:

- In case the subject has already completed visit 2, the end-of-study visit would correspond to Visit 3,
- In case the subject has not completed visit 2, the end-of-study visit would correspond to the Termination Visit. Subject not fulfilling criteria for continuation at V2 will complete the TV.

If possible, the IP should be returned by the subject. Subjects who discontinue due to safety reasons should, whenever possible, be seen and assessed by the investigator and be medically advised as appropriate.

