### 15.3 SAMPLE SIZE CALCULATION

The sample size for the present study is calculated so that the comparison of the verum treatment group and the placebo treatment group for the primary endpoint has 90% power to detect a relevant clinical effect size  $\delta$  (i.e., the ratio of the absolute val-

ue of the difference between two means and the standard deviation) with a two-sided significance level  $\alpha=0.05$  as outlined below.

Based on the results of a previously conducted trial with the same IP in a comparable setting (sponsor's data on file), the difference between the verum group and the placebo group regarding the mean AUC of the WURSS-21 QoL composite subscore during first 8 days of symptoms is expected to be at least 33.900. The associated common standard deviation  $\sigma$  is expected to be 92.700. Therefore, the relevant clinical effect size  $\delta = |\mu_{\text{verum}} - \mu_{\text{placebo}}| / \sigma$  (i.e. the ratio of the difference between verum and placebo and the standard deviation) which should be detected with adequate power is assumed to be 0.366. This corresponds to  $p_1 = P(X < Y) = 0.602$  which is the probability that an observation, X, in group 1 will be less than an observation Y in group 2 when the alternative hypothesis is true. The null hypothesis being tested is that  $p_1 = 0.5$ .

Under these assumptions, a sample size of  $n = 169$  subjects in each treatment group will have 90% power to detect a probability of 0.602 that an observation in the verum group is less than an observation in the placebo group using a Wilcoxon (Mann-Whitney) rank-sum test with a 0.05 two-sided significance level (nQuery Advisor® Release 7.0).

Based on the sample size in the study and taking into account an assumption for a power of 80%, an effect size of 0.315 with regard to the main secondary endpoints (Jackson score AUC and exposure to relevant concomitant medication) would be detectable (with a power of 80% and a sample size of  $n = 169$  subjects in each treatment group,  $p_1 = P(X < Y) = 0.588$  is calculated, corresponding to an effect size  $d = 0.315$ .)

Thus, considering the planned 1:1 randomization with two treatment groups,  $n = 338$  subjects (with  $n = 169$  subjects per treatment group) are required for the primary confirmatory statistical analysis of the study.

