## 15.10 ANALYSIS OF MAJOR SECONDARY ENDPOINTS

The major secondary endpoints are ranked according to clinical relevance as:

1. AUC days 1-8 composite daily severity of all symptoms within the Jackson score (mean of morning and evening) (day 1 is the first day of symptom recording). The two-sided confirmatory null-hypothesis will be tested with the non-parametric two-sided Wilcoxon (Mann-Whitney) rank-sum test.
2. Exposure to any concomitant treatment (including natural health products) that may affect common cold symptoms - immune suppressants/immune stimulants, analgesics/anti-rheumatics, anti-phlogistics, antitussives/expectorants, mouth or throat therapeutics, decongestants, antibiotics, anti-histaminergic drugs, nasal drops/spray or any medication/treatment known to affect common cold symptoms - at any dose, expressed as number of days with concomitant treatment during the first 4 days for each subject (based on diary data). The two-sided confirmatory null-hypothesis for the second major secondary endpoint will be tested using the non-parametric two-sided Wilcoxon (Mann-Whitney) rank-sum test.

In order to control the overall type I error rate, the primary endpoint and the two major secondary endpoints will be tested in a fixed sequence as a-priori ordered hypotheses. That is, the first major secondary endpoint will be tested only if the primary endpoint is positive (ie,  $p < 0.05$ ), and the second major secondary endpoint will be tested

only if the first major secondary endpoint is positive. No confirmatory claims will be based on endpoints that have a rank lower than or equal to that variable whose null hypothesis is the first that could not be rejected.

The confirmatory analysis of the major secondary endpoints will be performed for the full analysis set. Exploratory analyses will be performed for the per-protocol analysis set.

Data of the major secondary endpoints will be summarized by descriptive statistics using appropriate tabulation.

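### Use of a prohibited cold remedy counts toward a confirmatory endpoint and is also a possible ground for withdrawal, so a treated subject can leave the full analysis set for a post-randomisation reason

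*Protocol*

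**What the plan says.** - **Endpoint.** Section 15.10 makes exposure to concomitant cold treatment the second major secondary endpoint, "expressed as number of days with concomitant treatment during the first 4 days for each subject". It is confirmatory, third in the fixed sequence, and tested on the FAS. It counts any dose of the listed classes, so permitted rescue and prohibited products both score.
- **Prohibition.** Section 12: "During the study, the following concomitant treatment listed in the exclusion criteria should not be used". The classes that follow are those of the endpoint. Defined rescue (paracetamol, ibuprofen, saline nasal products, and antibiotics for another ailment) is exempt.
- **Withdrawal.** Section 13.8.1 gives, as one example of a reason, "intake of concurrent medication according to exclusion criteria, which could influence the results of the study". A subject who stops early is asked to attend an end-of-study visit corresponding to V3 or the termination visit. The diary is returned at either (Sections 13.2.2 and 13.3).
- **Replacement.** Section 15.4: "Drop-outs after V2 will be replaced", up to 400 subjects completing V2 and V3.
- **FAS.** Section 15.5 requires treatment and an available primary endpoint. It then removes one further group, though these subjects stay in the treated set: "Subjects which have not been enrolled in the study according to the inclusion/exclusion criteria, but this had only been detected during the study" or in data cleaning.
- **Deviations.** Section 15.6 grades violations of the inclusion and exclusion criteria as minor or major, and sends relevant deviations to exclusion from the per-protocol set.
- **Criteria that run on.** Exclusion criterion 3 reads "Influenza vaccination within the last 3 months prior to V1 and during the study". Criterion 9 (another clinical study) also extends into the study.

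**The concern.** A behaviour that the trial measures as an outcome can also end the measurement. A subject who feels worse is plausibly more likely to reach for a decongestant or cough remedy. If that leads to early withdrawal, the subject's AUC and remedy-use count are both lost from the set on which the confirmatory tests are run. Membership of the FAS then depends on something that happens after randomisation and may be affected by treatment. If the product works, more placebo than verum subjects would go. That would shrink the observed difference in the primary endpoint and cut off the upper end of the remedy-use endpoint. Replacement restores the count but not the comparison of the groups as randomised.

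**Working it through.** **1. The route, section by section.**
- V2 falls 1–3 days after symptom start, and the diary and concomitant treatment are reviewed there (Sections 13.2.1 and 13.6.2). Prohibited use can therefore come to light inside the 4-day window and before day 8.
- If the investigator then withdraws the subject and the end-of-study visit is held early, the diary comes back. Nothing in the protocol continues it to day 8.
- A diary ending around days 2–4 gives no observed day 1–8 AUC, so the availability clause of Section 15.5 can exclude the subject.
- Replacement follows for drop-outs after V2. It is unclear whether an early end-of-study visit that stands in for V3 counts as completing V3, so both cases are shown below.

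**2. The eligibility wording.** Criterion 4 covers only regular use in the 4 weeks before V1, and inclusion criterion 4 is readiness to comply. Yet Sections 12 and 13.8.1 tie on-study use to the exclusion criteria. Criteria 3 and 9 extend into the study, which cannot be judged at enrolment. For an eligibility violation, Section 15.5 points to the FAS and Section 15.6 to the per-protocol set.

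**3. The plan's own figure (Section 15.3).** Inputs: mean difference 33.900, SD 92.700, and a "rank-sum test with a 0.05 two-sided significance level".
- d = 33.9/92.7 = 0.366; p1 = Φ(d/√2) = 0.602.
- Noether: n per group = (1.960 + 1.282)² / [6 × (0.602 − 0.5)²] = 168.3, rounded up to 169. This reproduces the statement that 169 "subjects in each treatment group will have 90% power to detect a probability of 0.602".
- 2 × 169 = 338, and 338 × 1.18 = 398.8, stated as 400. The margin is 62 subjects, or 15.5% of 400.
- With power = Φ(√(6n) × 0.102 − 1.960), 200 per group gives 0.942.

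**4. Size under assumption.** The documents give no rate of remedy-related withdrawal. The rates below are assumptions, set wide.
- Model: normal AUC, d = 0.366, 200 per group. The probability of loss is logistic in AUC: 10–30% at the placebo mean, log-odds rising 1.0–1.5 per SD. Wilcoxon test, 1,500 replicates.
- Loss: about 14–35% of placebo and 10–27% of verum subjects. That is 28 + 20 = 48 up to 70 + 54 = 124 of 400, leaving 352 down to 276.
- Mean difference: from 0.366 to about 0.34–0.28 SD. In AUC units (× 92.7), 33.9 falls to about 31.5–26.0.
- Power without replacement: about 0.91–0.73. With replacement to 400: about 0.93–0.87. A second run of 4,000 replicates gave 0.90–0.74 and 0.92–0.88.
- Loss of the same size unrelated to outcome, from the formula in step 3: 0.91 at 176 per group and 0.84 at 138. At the heavy end, about half the drop from 0.94 to 0.73 is lost numbers and half is selection.
- No treatment effect, same rule in both groups: rejection stays at about 0.05.

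**5. A harsher variant.** If the worst 10% or 20% are removed by one common cut-off without replacement, power is 0.82 or 0.68 and the mean difference 0.26 or 0.21 SD. With a skewed (lognormal) AUC and a proportional effect, removing 20% leaves power at 0.94, but the mean difference falls to 0.11 SD. Dilution appears under every model tried. The loss of power depends on the model.

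**The case against.** Four counter-arguments have force.

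- **The eligibility sentence.** A reader might infer that Section 15.5 expels anyone who takes a remedy. It does not. It concerns wrong enrolment found late. Remedy use during a cold is a protocol deviation, which Section 15.6 sends to the per-protocol set. Criteria 3 and 9 do run into the study, but vaccination and joining another trial are not driven by how bad the cold is.
- **Rescue is exempt.** A subject with a bad cold can take paracetamol, ibuprofen or saline, score on the endpoint and breach nothing. Only the non-rescue part of the counted use is in conflict.
- **Withdrawal is optional.** Section 13.8.1 offers examples only, and the continuation rule in Section 10.3 has no condition on remedy use. Use recorded after V2 would normally be seen at V3, 16 ± 4 days after symptom start, when days 1–8 are already complete. A reader might infer that the worst colds do leave the FAS. The documents support only that some could.
- **Missing data belong to the SAP.** Section 15.15 defers their handling, and the SAP may accept a partial diary as an available AUC.

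The first three narrow the point and are accepted. The fourth stands only in part: the protocol itself fixes the availability clause, the withdrawal ground and replacement, and an SAP written after blinded review cannot recover diary days that were never collected. Nor do the documents support reading this as a risk of a false positive: set allocation is agreed before unblinding, and a common rule leaves type I error near 0.05.

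**Conclusion.** The point holds as a possibility left open by the text. Use of a non-rescue remedy counts toward a confirmatory endpoint, is prohibited, and may lead to withdrawal. Through the availability clause, an early withdrawal can remove a treated subject from the FAS. Separately, Sections 15.5 and 15.6 give different consequences for an eligibility violation, and two criteria cannot be judged at enrolment.

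The actual size is unknown. The estimates rest on assumed loss rates, an assumed link between severity and loss, a normal AUC and the planned effect. Under them the observed difference shrinks by about 7–23% (0.34/0.366 and 0.28/0.366). Once subjects are replaced, power stays close to the planned 90%. The harm is a diluted effect estimate and a truncated secondary endpoint. If such withdrawals are rare, or are found only at V3, the effect is negligible.

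**What to change.** - **Section 15.5.** Limit eligibility-based exclusions from the FAS to criteria that can be assessed before randomisation. State that on-study concomitant treatment, vaccination or non-compliance alone affects the per-protocol set only, in line with Section 15.6.
- **Section 13.8.1.** State that diary collection continues to day 8 after withdrawal where the subject agrees, and that these data enter the FAS.
- **Reconcile** Sections 10.4, 12, 13.8.1, 15.5, 15.6 and 15.10, so that each uses the same terms for prohibited use, rescue use and eligibility. Whether a subject continues the product is a clinical matter and is not addressed here.

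The cost is a few sentences and a few more diaries to collect. The small downside is that some subjects with deviations remain in the FAS; the per-protocol analysis already covers that question.

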## 15.6 ELIGIBILITY, PROTOCOL DEVIATIONS

A detailed description of the procedures and criteria used for data review and sort out will be provided prior to start of the analysis and before unblinding of the treatment allocation.

Each subject's allocation to the different analysis sets will be identified and mutually agreed upon during data review prior to unblinding of the treatment allocation. Deviations from the protocol including violations of inclusion/exclusion criteria will be assessed as 'minor' or 'major' based on the conjoint decisions according to the specifications outlined in the SAP or a separate document.

Relevant deviations from the protocol will lead to the exclusion of a subject from the per-protocol analysis set. Listings will be prepared to show the eligibility of all subjects for the different analysis sets and a summary will be given on the number of subjects per analysis set.

## 15.7 DEMOGRAPHICS AND OTHER BASELINE CHARACTERISTICS

Demographics and other baseline characteristics will be summarized by means of descriptive statistics for continuous data and frequency tables for categorical data. Summary tables will be provided for all analysis sets.

## 15.8 ASSESSMENT OF COMPLIANCE

Evaluation of overall compliance with respect to IP use will be based on the return and documentation of unused IP (per vial weight) as compared to duration of the period defined for IP usage (see chapter 11.9.1). Assessment of compliance to start of IP use and to start of filling out the subject cold diary is described in chapters 11.9.2 and 11.9.3. Compliance data will be summarized by means of descriptive statistics for continuous data and frequency tables for categorical data for all analysis sets besides the all subjects randomized set.

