### **11.9.2 Compliance at the Start of IP use**

The IP use should start when the following conditions have been fulfilled:

- answering "Yes" to either of the questions in the subject daily diary: "Do you think/feel you have a cold?" or "Do you think/feel you are coming down with a cold (might be having first signs of cold)?" AND
- Jackson score of at least 1 in the subject's cold diary (mild = present, but not disturbing or irritating) for any symptom except headache

A subject is classified as compliant when applying the IP by the morning of the next day after the first day of a defined common cold (Jackson score  $\geq 1$ , except headache).

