### **11.9.3 Compliance at the Start of Filling out the Subject Cold Diary**

The subjects have to start filling out the cold diary on the first day they answer "Yes" to either of the questions in the subject daily diary: "Do you think/feel you have a cold?" or "Do you think/feel you are coming down with a cold (might be having first signs of cold)?".

A subject is classified as compliant when starting records in the cold diary by the morning of the next day after they answer "Yes" to the above questions in the evening.

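### Start-of-use compliance is tabulated only among subjects who took at least one dose, so those who should have started and never did are left out, and diary-start compliance is reported in the wrong population

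*Protocol*

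**What the plan says.** Section 11.9 defines three compliance measures. Overall use (11.9.1) rests on returned vial weight. For start of use (11.9.2), once a subject has answered yes to a cold question and has scored at least 1 on the Jackson scale for a symptom other than headache, that subject is "classified as compliant when applying the IP by the morning of the next day after the first day of a defined common cold". For the cold diary (11.9.3), the subject must begin on the first day of a yes answer, and the rule reads: "A subject is classified as compliant when starting records in the cold diary by the morning of the next day" after an evening yes. No dose enters this last rule.

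Section 15.8 then has all compliance data summarised "for all analysis sets besides the all subjects randomized set". The sets that remain are defined in section 15.5:

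- treated set, the widest of the three: "All subjects of the all subjects treated set which received at least 1 dose of the IP"
- full analysis set: drawn from the treated set, limited to those with a value for the primary endpoint
- per-protocol set: "All subjects of the full analysis set without any major violation of the protocol and its procedures"

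The first definition refers to itself, but section 15.12 describes the same population as those treated at least once, so the one-dose reading is safe.

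Section 15.5 also says of the treated-only analysis: "The decision of whether or not to begin treatment could not be influenced by knowledge of the assigned treatment".

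**The concern.** A rate of compliance with starting a product should have as its denominator everyone who was due to start. Here the denominator is limited to people who did start at some point. Late starters stay in and count against the rate. Subjects who never started, the most complete failures under 11.9.2, drop out.

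The diary measure has a different problem. Its own definition covers every subject who answered yes, whether or not a dose was taken, yet it is reported only among those who took one.

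What is at stake is the accuracy of two descriptive figures. The missing denominator would also be useful elsewhere. Efficacy is analysed in treated subjects only, on the argument that blinding keeps the decision to start independent of arm. The proportion starting among those who met the start conditions, by arm, speaks directly to that argument, and section 15.8 plans no such summary.

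**Working it through.** **Plan figures.** The protocol states no compliance rate and no number of subjects who met the start conditions without using the product. The one usable figure is the 400 treated subjects in section 15.3. It reproduces: 338 × 1.18 = 398.84, rounded to 400. With 600 randomised (section 10.1), about 600 − 400 = 200 are expected to be untreated. How many of these had a triggering cold is not given.

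**Start of use (11.9.2).** Let T be treated subjects, C those among them who started on time, and K those who met both start conditions but never sprayed.

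- Rate as planned: C / T
- Rate among all who were due to start: C / (T + K), since no never-starter can satisfy the rule
- Overstatement, with c = C / T: c × K / (T + K)

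This is positive whenever K > 0 and C > 0, so the direction is fixed. For T = 400 (plan) and assumed c and K:

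| Treated-set rate c (assumed) | K = 4 | K = 20 | K = 40 |
|---|---|---|---|
| 80% | 79.2% | 76.2% | 72.7% |
| 90% | 89.1% | 85.7% | 81.8% |
| 95% | 94.1% | 90.5% | 86.4% |

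At c = 90%, C = 360. The three results are 360/404, 360/420 and 360/440, giving overstatements of 0.9, 4.3 and 8.2 points.

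**Diary start (11.9.3).** Here K stands for untreated subjects who answered yes, and q for the share of them who began the diary on time.

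- Rate as planned: C / T
- Rate in the population of the definition: (C + qK) / (T + K)

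With T = 400, c = 90% and K = 20:

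- q = 0: 360/420 = 85.7%
- q = 0.90: 378/420 = 90.0%
- q = 1: 380/420 = 90.5%

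So the treated-set rate is too high, right or too low according to whether q is below, equal to or above 90%. With q = 1 and K from 4 to 40, the full rate is 364/404 = 90.1% to 400/440 = 90.9%, an understatement of 0.1 to 0.9 points.

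The protocol does not settle q. A subject who met both start conditions must already have a Jackson score in the cold diary, which points to a high q. A subject who answered yes and never opened the cold diary could not properly trigger use, and is likely to be untreated, which points to a low q. Both kinds are excluded.

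**The case against.** Several points on the other side stand.

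- A reader might infer that both rates are overstated. The documents do not support that for the diary. Its rule involves no dose, and anyone who met both start conditions has a cold-diary entry.
- A reader might also infer that diary-start compliance must come out near 100% because treatment and the AUC depend on the diary. That is too strong. The rule concerns timing, late diary starters can still be treated, and day 1 of the AUC is the first day of recording (synopsis), so a late start does not remove the AUC.
- It would be wrong to say that nothing else bears on who starts treatment. Section 15.5 requires a flowchart by treatment group with reasons for exclusion, and baseline tables for all four sets. Section 15.6 adds listings of eligibility. These show untreated subjects by arm. The text does not say that they separate subjects without a cold from subjects who met the start conditions and did not start.
- Section 15.3 expects the ratio to depart from 1:1 because only those with symptoms will start, not because subjects decline to start.
- Leaving out the whole randomised set is reasonable in itself, since start compliance is undefined for someone who never had symptoms. The better denominator is triggered subjects, not all randomised.
- The number of never-starters may be close to zero.

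The further defence, that details are left to the SAP, does not answer the point. Section 15.8 itself fixes which sets are used.

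**Conclusion.** The point holds for start of use. As section 15.8 is written, subjects who met both start conditions and never sprayed cannot count as non-compliant, and the rate is overstated if there is even one. The size is unknown: 0.9 to 8.2 points for an assumed 4 to 40 never-starters against 400 treated, at an assumed 90%.

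For diary start, the documents support only that the rate is reported in a population other than the one it is defined for, with bias of unknown direction.

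A reader might go further and infer that the primary analysis is compromised. Nothing here shows that. The summaries are descriptive, and the endpoints, the full analysis set, the sample size and the confirmatory tests are unaffected. The severity is minor.

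**What to change.** Keep the tables that section 15.8 plans, and add one table by arm with these rows:

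1. Start-of-use compliance (11.9.2) among all randomised subjects whose diary met both start conditions, with never-starters counted as non-compliant. Subjects withdrawn because the target number of treated subjects had been reached (section 13.8.1) are listed separately, so that they are not misclassified.
2. Diary-start compliance (11.9.3) among all randomised subjects who answered yes to either cold question.
3. The proportion starting the product among subjects who met both start conditions, with the between-arm difference and a 95% confidence interval. This is a descriptive check on the section 15.5 statement about starting treatment, and it supplements the flowchart.

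Vial-weight compliance (11.9.1) stays as planned.

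No new data are needed. The daily diary runs from V1 (section 13.6.1) and is returned at V3 or at the Termination Visit (sections 13.2.2 and 13.3). The cost is a short addition to section 15.8 or the SAP, one table, and possibly a slightly lower reported compliance.
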